## 5. SELECTION AND WITHDRAWAL OF PARTICIPANTS

### Inclusion

Women who have a diagnosis of acute leukaemia (AL) or high-risk myelodysplasia (MDS) in pregnancy, or who have later conceived after receiving previous treatment for either AL or high-risk MDS.

### Exclusion

Pregnant women not meeting the inclusion criterion.

### Consent

This study is an observational cohort, recording routinely collected data from patient clinical records only. It will not be practicable to obtain consent for data collection from all women due to the sensitivity of subject, as some women will no longer be in routine clinical care or may have died. To ensure the data collected is informative as possible, we need to aim for 100% collection.

Consent will be sought for:

#### **Current cases**

1. Where patients are currently receiving treatment and are **now** pregnant

Or

2. Where patients have previously received treatment and are **now** pregnant.

#### **Historical cases**

1. Where patients had treatment whilst pregnant and are still in active follow up and/or contact with the clinical care team.

Or

2. Where patients had a previous AL diagnosis and subsequently became pregnant post treatment that are still in active follow up and/or contact with the clinical care team.

For historical cases where the patient had treatment whilst pregnant or subsequently became pregnant post treatment but are now:

- a) No longer in active clinical follow up. This may include: Discharged – either following treatment complete or as a result of non-attendance (DNA) of clinic appointments
- b) No longer in contact with the clinical care team
- c) Known to have died

Identifiable data will be collected without consent subject to the relevant approvals being given. Due to the sensitivity of the condition, contacting patients for consent if no longer in contact with the clinical care team could possibly cause unnecessary emotional distress to the patient and/or the family as some patients and/or their babies will not have survived.

Participants have no direct involvement in the study and will not be contacted directly beyond consent (if applicable). No site information or personal identifiable information will be contained within the analysis dataset. Data collection forms will be completed by the clinical research team who have permission to access their clinical data at the site as part of the usual care of the patient.

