## 6. ASSESSMENTS AND PROCEDURES

[figure not shown]

Once a case is identified, if the case is **current or the patient is still in active follow up or still in regular contact with the clinical care team**, the Consultant haematologist/designated person from the local clinical study team will provide the patient with the Participant Information Sheet, discuss the study and answer any questions the patient may have. Consent will then be sought with the option for the patient to consent on the day. If the patient requests further time to consider we will arrange a more convenient time for them to come back and complete the consent process. If the case involves a **patient who has been discharged from active follow up, is no longer in contact with the clinical team or it is known the patient has died**, the data will be processed without consent providing they have not previously expressed a wish for their data to be used for the purposes of research. As HHTU will not be collecting any directly identifiable data, this will be done in accordance with each site's own local policy.

Once an eligible case is confirmed, the Consultant haematologist/designated person from the local clinical study team will log into RCC, HHTU's secure online database and complete the relevant electronic case report forms (eCRFs). A screening form will be completed for all, which will record the consent status (Yes/No/Not applicable). Depending on consent status ("Yes" or "not applicable"), the system will automatically generate a unique patient ID and more detailed eCRFs will be activated accordingly. For those not consenting, reason given for declining will be recorded on the screening CRF. When consent is required, scanned copies of the signed written informed consent form will be uploaded to RCC as part of the subject details eCRF. Further eCRFs will not be opened until the consent form is uploaded. RCC will **partition the identifiable data within the system**.

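### In historical cases, refusal of consent can remove only women who are alive, so any refusal pushes maternal mortality among entered cases upward

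*Protocol*

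**What the plan says.** The primary outcome in Section 2 is what happens to mothers and babies. Section 4 adds retrospective cases since August 2009, before and after the 2015 guideline, as comparators for judging its impact. On completeness, the Consent part of Section 5 says "we need to aim for 100% collection".

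Entry of a historical case depends on the woman's status when the case is identified:

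- **Consent needed.** "Where patients had treatment whilst pregnant and are still in active follow up and/or contact with the clinical care team"; and, for the other cohort, "Where patients had a previous AL diagnosis and subsequently became pregnant post treatment that are still in active follow up and/or contact".
- **Consent not needed.** Women discharged, out of contact, or "Known to have died". For these, "Identifiable data will be collected without consent subject to the relevant approvals being given".

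Section 6 repeats the exemption with a proviso: "the data will be processed without consent providing they have not previously expressed a wish for their data to be used" in research. As printed this bars women who had agreed to research use and admits those who had objected, so a second negative seems to be missing.

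Section 6 also says what follows a refusal. "A screening form will be completed for all, which will record the consent status (Yes/No/Not applicable"). A patient ID and the detailed forms are generated only for Yes or Not applicable, and where consent is needed, "Further eCRFs will not be opened until the consent form is uploaded". For a woman who declines, the protocol mentions only her consent status and her reason.

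**The concern.** Inclusion of a historical case is tied to maternal survival, which is part of the primary outcome. A woman who died cannot be lost through refusal, because nobody is asked. A woman who lived and is still in contact can be. Every refusal therefore takes a survivor out of the denominator and leaves the numerator unchanged.

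Current cases differ: consent is sought while the woman is pregnant, before most of her outcome is known. Historical and prospective mortality are thus not selected in the same way. Nothing in the protocol acknowledges the asymmetry or says that decliners will be counted as alive. What the screening form records about decliners is settled when data are collected, and a later analysis plan cannot recover items that were never entered.

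**Working it through.** The protocol states no mortality, refusal rate or share of survivors in contact, so it has no figure to reproduce. The inputs below are assumptions, shown over a range.

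**Inputs**
- *m*: true maternal mortality among historical cases (assumed).
- *f*: share of survivors still in follow-up or contact, who must consent under Section 5 (assumed).
- *d*: share of those women who do not consent (assumed).
- Deaths and out-of-contact survivors are taken as entered in full.

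**Formula.** Deaths entered are proportional to *m*, and survivors entered to (1 − *m*)(1 − *fd*). So

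observed mortality = *m* / [*m* + (1 − *m*)(1 − *fd*)].

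This exceeds *m* whenever *fd* > 0 and equals *m* only when nobody refuses.

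**True mortality 40%**

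| *f* | *d* | Calculation | Observed |
|---|---|---|---|
| 0.5 | 5% | 0.4 / (0.4 + 0.6 × 0.975) = 0.4/0.985 | 40.6% |
| 0.5 | 20% | 0.4 / (0.4 + 0.6 × 0.90) = 0.4/0.94 | 42.6% |
| 1.0 | 20% | 0.4 / (0.4 + 0.6 × 0.80) = 0.4/0.88 | 45.5% |
| 0.5 | 30% | 0.4 / (0.4 + 0.6 × 0.85) = 0.4/0.91 | 44.0% |
| 1.0 | 30% | 0.4 / (0.4 + 0.6 × 0.70) = 0.4/0.82 | 48.8% |

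**Other levels of true mortality**

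| True | *f* = 0.3, *d* = 5% | *f* = 0.6, *d* = 20% | *f* = 1, *d* = 30% |
|---|---|---|---|
| 10% | 10.1% | 11.2% | 13.7% |
| 30% | 30.3% | 32.8% | 38.0% |
| 50% | 50.4% | 53.2% | 58.8% |

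The 10% row is a reminder that mortality may differ by cohort: women who conceived after treatment had to survive it to qualify.

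**Guideline periods.** Suppose true mortality is 40% in both periods and 20% refuse, but 30% of survivors are in contact before the guideline and 90% after (assumed). Observed mortality is 0.4/(0.4 + 0.6 × 0.94) = 41.5% before and 0.4/(0.4 + 0.6 × 0.82) = 44.8% after: a difference of 3.3 points with no true change. With equal contact shares, refusal rates and true mortality there would be none.

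**Restoring the decliners.** Take an assumed 100 historical cases with *m* = 30%, *f* = 0.6, *d* = 20%. There are 30 deaths, 70 survivors, 42 in contact and 8.4 decliners on average. Over entered cases, mortality is 30/91.6 = 32.8%. With decliners put back as alive at approach, it is 30/100 = 30.0%.

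**The prior-wish proviso.** If it is meant to exclude women who had objected, it could also remove some deaths. With no such exclusions among out-of-contact survivors, the upward shift is cancelled only if the share of deaths excluded equals *fd*. In the last example that is 0.6 × 0.2 = 12%. At 2% of deaths excluded, observed mortality falls only from 32.8% to 32.3%.

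**The case against.** The strongest reply is that this belongs in the statistical analysis plan. Section 7 promises one before analysis, the protocol fixes no denominator for mortality, and the screening form already lets decliners be counted. That holds for the choice of denominator and the extra presentation. It does not hold for the entry rule, or for what the form captures about decliners.

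A reader might infer several stronger things that the documents do not support:

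- **That historical mortality will be overstated overall.** Only one mechanism is shown. Clinicians reporting back to 2009 may miss deaths or survivors, with an error in either direction.
- **That the effect is large.** The study uses records only, with no contact beyond consent, so low refusal is plausible. Survivors who are discharged or out of contact enter without consent, which dilutes the effect. It is below 1 point when refusals are few and many survivors are out of contact.
- **That no death can be excluded, or that complete collection is achieved for deaths.** Deaths still depend on clinician reporting, on approvals and on the prior-wish proviso.
- **That the two guideline periods are biased differently.** The same consent rule applies to both. A difference arises only if contact shares, refusal rates or true mortality differ, and the documents give none of these.

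The ethical reason for not approaching families of women who died is sound, and nothing here asks to change it.

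**Conclusion.** The point holds as a known direction with an unknown size. Refusal at approach can remove only living women, so any refusal biases historical maternal mortality over entered cases upward. At an assumed true mortality of 40% the shift runs from 0.6 points (5% refusal, half of survivors in contact) to 8.8 points (30% refusal, all in contact). These figures rest wholly on assumed refusal and contact shares and isolate refusal from other reporting errors. Distortion of the pre/post-guideline comparison is possible, not shown. It is worth correcting because it touches the primary outcome and most of what is needed is already planned.

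**What to change.** 1. Add two non-identifying tick boxes to the screening form: cohort (diagnosed in pregnancy, or conceived after treatment) and period (before or after the guideline). They would be completed for decliners too, so the ethics approval should cover them.
2. Report the number of decliners by cohort and period. Do not report them by site: Sections 5 and 9 keep site out of the analysis dataset, and small cells could identify women who refused.
3. Present historical maternal mortality twice: over entered cases, and with decliners added to the denominator as alive at the date of approach.
4. Reconcile the wording of the prior-wish proviso in Section 6 with its evident purpose, and with Section 5, which does not mention it.

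The cost is two items on a form already completed for everyone, their approval, and one extra table row. The limit is that this corrects refusal selection for vital status at approach only. It does not correct baby outcomes, later deaths, survival at fixed 2- or 4-year points, or under-reporting by clinicians.

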## 6. ASSESSMENTS AND PROCEDURES

[figure not shown]

Once a case is identified, if the case is **current or the patient is still in active follow up or still in regular contact with the clinical care team**, the Consultant haematologist/designated person from the local clinical study team will provide the patient with the Participant Information Sheet, discuss the study and answer any questions the patient may have. Consent will then be sought with the option for the patient to consent on the day. If the patient requests further time to consider we will arrange a more convenient time for them to come back and complete the consent process. If the case involves a **patient who has been discharged from active follow up, is no longer in contact with the clinical team or it is known the patient has died**, the data will be processed without consent providing they have not previously expressed a wish for their data to be used for the purposes of research. As HHTU will not be collecting any directly identifiable data, this will be done in accordance with each site's own local policy.

Once an eligible case is confirmed, the Consultant haematologist/designated person from the local clinical study team will log into RCC, HHTU's secure online database and complete the relevant electronic case report forms (eCRFs). A screening form will be completed for all, which will record the consent status (Yes/No/Not applicable). Depending on consent status ("Yes" or "not applicable"), the system will automatically generate a unique patient ID and more detailed eCRFs will be activated accordingly. For those not consenting, reason given for declining will be recorded on the screening CRF. When consent is required, scanned copies of the signed written informed consent form will be uploaded to RCC as part of the subject details eCRF. Further eCRFs will not be opened until the consent form is uploaded. RCC will **partition the identifiable data within the system**.

In order to maintain patient confidentiality, no addresses, postcodes, hospital or NHS numbers will be collected within the database. However, data will be linked in an anonymised format in order for participating sites to obtain further information from clinical records and to complete follow-up data collection forms at the appropriate time points. Individual sites contributing data will maintain a code sheet linking the patient study number to identifiable data, which they will store according to their local data protection policies.

More detailed eCRFs relate to the initial AL diagnosis for those patients diagnosed during pregnancy, or prior to pregnancy. Further eCRFs will then be completed at appropriate time points to allow data to be subsequently collected from each patient upon completion of therapy, after the expected delivery date (if not already captured within the 'completion of therapy' time-point) and then for 2 defined follow-up data collections. For patients with previous AL, pregnancy, delivery and follow-up information will be collected. The specific data to be collected will enable effective assessment of current management practices for these patients and will allow us to ascertain the rate of successful outcomes of both mothers and neonates, as well as to determine the safety and related toxicities of any chemotherapy administered.

---

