We will use similar methodology to collect both retrospective and prospective data. Consultant haematologists will receive a reminder every 3 months via email. The email will include a link to the HHTU electronic data capture system where they will be able to submit any cases, either current or historical, into the study database. Once a case is identified, current patients or historical cases where the patient is still in active follow up or in regular contact with the clinical care team will be approached for consent. In historical cases where the patient is no longer in active follow-up or in regular contact with the clinical care team, cases will be processed without consent subject to the relevant approvals being gained.

Each patient entered onto the database will be designated a unique study identification number, generated automatically by the data capture system. Different case report forms will be activated accordingly as data is entered onto the system. Data will be entered directly into the database by the consultant haematologist through reference to medical records only, there will be no direct contact with patients. All data will be reported anonymously using the patient ID.

During the study set-up phase, consultant haematologists will be asked to provide an estimate of the number of cases encountered in the past ten years to enable a HHTU Trial Manager to monitor overall data collection rates. Email reminders will be issued, or the Local Clinical Research Team will be contacted by telephone, in order to minimise loss to follow-up. If a consultant haematologist is unwilling or too busy to provide a response, efforts will be made to identify an alternative suitable reporting individual at that site (e.g. an obstetrician) who would be part of the usual care team.

---

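### Protocol section 6 states the condition for using historical data without consent backwards: as worded it admits women who objected and shuts out women who agreed.

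*Protocol*

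**What the plan says.** The protocol describes the no-consent route for historical cases in three places.

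- Section 4 (Study Design) says that where the patient is no longer in follow-up or regular contact, "cases will be processed without consent subject to the relevant approvals being gained".
- Section 5 (Consent, Historical cases) says of women no longer in follow-up, out of contact or dead: "Identifiable data will be collected without consent subject to the relevant approvals being given".
- Section 6 (Assessments and Procedures) covers women who were discharged, have lost touch with the team or have died, and allows their records to be "processed without consent providing they have not previously expressed a wish for their data to be used for the purposes of research". It then adds, on the ground that the trials unit will hold nothing directly identifying, that "this will be done in accordance with each site's own local policy".

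Section 6 also describes how a case is opened in the database. A screening form is completed for everyone, with consent status recorded as Yes, No or Not applicable. For Yes or Not applicable, "the system will automatically generate a unique patient ID and more detailed eCRFs will be activated accordingly". Where a woman is asked and declines, the detailed forms are not opened: "For those not consenting, reason given for declining will be recorded on the screening CRF". Section 14 lists three national bodies whose approval is needed for using historical personal data without consent.

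**The concern.** The section 6 clause is meant as a safeguard, but its logic runs the wrong way. It makes the absence of a wish *for* research use the condition for processing, where a safeguard would require the absence of an objection.

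Historical women known to have died can enter the cohort only by this route, as can those who are both discharged and out of contact. The primary outcome is what happened to mothers and babies, so the sentence governs whether historical maternal deaths are counted. Two things are at stake. The first is ethical: the written protocol permits processing the data of a woman who had objected. The second concerns who enters the cohort: women who had agreed to research use are kept off the only route described for them.

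**Working it through.** No arithmetic applies. The plan states no figure on this point and none follows from it. The check is to run each kind of patient through the clause, then look for a correction elsewhere.

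**Step 1. The clause as written and with the negative restored**, for a woman who has died, or is discharged and out of contact:

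| Earlier wish on record | As written: condition met? | Result | With the negative restored: condition met? | Result |
|---|---|---|---|---|
| Wanted data used | No | Not processed by this route | Yes | Processed |
| Objected to use | Yes | Processed | No | Not processed |
| Nothing recorded | Yes | Processed | Yes | Processed |

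The first two rows swap and the third does not move. The error therefore affects only women with a recorded preference.

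**Step 2. Does another section correct it?** Sections 4 and 5 make the route conditional on approvals and say nothing about earlier wishes. Section 14 names the approving bodies but states no rule on objectors, and its approval dates are blank. No other sentence available states the opt-out the right way round. The section 6 figure is not reproduced in the text at hand, so it could not be checked.

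**Step 3. Would the database stop the error?** Not as described. A woman on the no-consent route would naturally be entered as Not applicable, and that status opens the detailed forms. No separate check for an earlier objection is described.

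**Step 4. What was intended?** Where consent is sought, a refusal keeps the forms closed. This points to an intention to respect objections, and so to a missing negative.

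**Step 5. Approvals and local policy.** Sections 4, 5 and 14 say what permits the processing. Section 6 refers the process to local policy and does not mention the approvals. The two can apply together, but the protocol does not say so. The reason section 6 gives, that nothing directly identifying is collected, also sits badly with section 5, which calls the same data identifiable. Section 9 lists the mother's year of birth, the child's date of birth and sex, and dates of death for these cases.

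**The case against.** The strongest reply is that this is a slip of one word with a plain intention behind it. The clause is introduced as a proviso, refusals are respected in the next paragraph, and most site staff would guess what was meant. Local policy or the approving bodies might also screen out objectors in practice. The analysis is mostly descriptive, with no strict sample size calculation, so no design figure is disturbed.

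Much of that stands. It is a drafting error rather than a deliberate choice, and nothing shows that any site would apply it literally. But a consent safeguard should not depend on staff disregarding its wording, and the protocol does not say that local policy or the approvals deal with objectors.

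The half about women who agreed is the softer one. The clause limits processing without consent, and an earlier wish for use might be argued to amount to consent. The protocol provides no such route for this group, so the gap remains. The half about women who objected holds on any literal reading.

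Three stronger readings are tempting and are not supported:

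- **A head count.** A reader might multiply the roughly 10 cases a year in section 7 by ten years, reach 10 × 10 = 100 historical cases, and treat some share of them as misclassified. The 10 a year is the expected number of *prospective* cases. Section 4 leaves the ten-year count to be estimated by haematologists during set-up, and women with no recorded wish are unaffected anyway.
- **All discharged survivors.** Sections 4 and 5 seek consent from historical patients still in contact with the care team, so some discharged women would be approached.
- **Two conflicting authorities.** A reader might infer that local policy replaces the national approvals, or that inclusion will vary by site. The two are compatible, and no section shows local policies that differ on inclusion.

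**Conclusion.** The point holds and should be corrected before the protocol is used. As worded, section 6 reverses the outcome for both kinds of woman with a recorded preference, and nothing in the available text puts it right. It is an operative entry rule, which is why a one-word slip matters.

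The size is limited and unknown. The number of affected women cannot be derived from the document and may be small. The conclusion rests on the literal wording and on the text available, which does not include the section 6 figure. The passage on local policy is a lesser matter: it needs clarifying, and it is not a contradiction in the rule for who may be included.

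**What to change.** Make three changes to section 6.

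1. Replace the proviso with: *provided there is no record that the patient objected to her data being used for research*.
2. State that a woman with a recorded objection is entered as No on the existing screening form, so that the detailed forms stay closed. This uses a field already planned; a separate tick box for prior objection is optional.
3. State that local site policy applies in addition to, and not instead of, the approvals required in sections 4, 5 and 14. While doing so, reconcile the remark that nothing directly identifying is collected with section 5, which describes the data as identifiable.

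Replacing local policy with the national approvals would not by itself produce one rule at every site: section 14 lists separate bodies for England and Wales, Scotland and Northern Ireland, and their conditions may differ.

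The cost is a few sentences of protocol text and a line of guidance for completing the screening form. No extra patients, data items or analyses are needed.
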